***Diagnosis of SSI:***

We adopted the Centers for Disease Control definition (CDC) to diagnose SSI(8):

Superficial SSI Infection is associated with skin and subcutaneous tissue within 30 days after surgery and at least one of the following:

Purulent drainage with or without culture confirmation

Positive tissue or fluid culture

Deep SSI Infection associated with deep tissues within 30 days after surgery and at least one of the following:

Purulent drainage from the deep incision.

A deep incision spontaneously dehisces or opened by the surgeon with at least one of fever, pain, tenderness—unless culture is negative

Radiologically or histologically detected abscess or deep infection

Diagnosis of deep incisional infection made by a surgeon or attending physician

***Follow up:***

Patients will be followed 30 days after surgery. Four visits were programmed after surgery :

**Check-up 1:** Two days after surgery.

**Check-up 2:** 7 days after surgery.

**Check-up 3:** 15 days after surgery.

**Check-up 4:** 30 days after surgery.

In each visit, wound surveillance will be performed by a resident, and if an SSI is suspected the wound will be photographed and the patient will be referred to a senior surgeon to confirm the diagnosis (figure2).

[figure not shown]

***Costs estimation:***

**Cesarian cost:** In all cases we will use a surgical bundle with fixed cost. The overall cost per procedure is calculated by the following formula:

**Cesarian cost = Bundle cost + Suture material cost + Hospital stay cost**.

**SSI cost:** A care bundle with fixed cost will be also used for wound care. The overall cost per SSI is calculated by the following formula:

**SSI cost = SSI bundle cost + Drugs cost + Investigation tests cost + Reintervention cost + Hospital stay cost.**

**Total cost (TC)**: The total cost is the sum of cesarian cost and SSI cost

**Total cost = Cesarian cost + SSI cost**

**Cost per SSI prevented = TC (Vicryl Plus) – TC (Vicryl) / SSI (Vicryl Plus) – SSI (Vicryl).**

**Limitations:**

The fact that the survey was carried out in a single public institution without extending to other health structures, constitutes one of the limitations of our study. Another limitation is that data were not computerized.

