**Data collection and management :**

For data collection we will use an anomymos canevas (Appendix 1), containing six sections: SSI risk factors / Admission / Operative procedure / follow up / SSI diagnosis and management / hospital cost.

Data were collected from: Prenatal follow-up records/ Obstetrical records /Surgical reports/Anesthesia reports/Post-operative monitoring records.

The confidentiality of the participants will be maintained at any time.

The following clinical characteristics will be collected : Age, smoking, Body mass index, presence of diabetes, presence of anemia and history of CD.

Risk factors related to the current pregnancy, will be collected : the presence of gestational diabetes (GDM), preeclampsia (PE) as well as the delay of premature rupture of membranes (PROM) if it exists.

The following information will be collected at the time of the operation : the nature of the caesarean section, operating time, operative complication, the Amerian Society of Anasthesiologist (ASA) score, and the use of an unloading drainage system.

During the postoperative visits, signs of surgical site infections will be cheked , the healing time and the quality of the scar at 30 days will also be noted.

In the presence of a SSI we note its nature, in-patient or out-patient management, antibiotic therapy used, local care kits, imaging examination requested, radiological drainage if needed and the frequency of investigation tests performed.

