**Outcomes :**

*Primary outcome:* The rate of SSIs within 30 days after surgery.

*Secondary outcomes*: The rate of wound healing complications.

The cost impact of triclosan coated suture use from a hospital perspective.

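### The total cost formula has no term for wound complications or suspected infections that fall short of the SSI definition, so hospital cost is incompletely measured

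*Protocol*

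**What the plan says.** The Outcomes section of the protocol lists two secondary outcomes. One is "The rate of wound healing complications"; the other is "The cost impact of triclosan coated suture use from a hospital perspective". The Hypotheses section states the economic hypothesis as a reduction in healthcare cost, without restricting it to infection.

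The Costs estimation section then fixes the arithmetic:

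- For every woman: "Cesarian cost = Bundle cost + Suture material cost + Hospital stay cost".
- For each infection: "SSI cost = SSI bundle cost + Drugs cost + Investigation tests cost + Reintervention cost + Hospital stay cost".
- Overall: "Total cost = Cesarian cost + SSI cost".

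This total is the quantity differenced in the numerator of the cost per SSI prevented.

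The Data collection and management section gives the trigger for recording treatment resources: "In the presence of a SSI we note its nature, in-patient or out-patient management, antibiotic therapy used, local care kits, imaging examination requested", followed by radiological drainage and the frequency of tests. For all women, the postoperative visits are said to record signs of SSI, healing time and scar quality at 30 days. No resource items are named there. The data form has a separate section for hospital cost, but the form itself (Appendix 1) is not visible.

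**The concern.** A hospital-perspective total should count what the hospital spends on the wound, whatever label the wound event receives. Here, drugs, tests, reintervention and any stay after the caesarean admission enter only through the per-SSI formula. A wound event that needs care but does not meet the criteria under Diagnosis of SSI contributes nothing beyond the caesarean cost. The same holds for a suspected SSI that is worked up and then not confirmed by the senior surgeon (Follow up section).

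The cost result is therefore tied to the SSI result and cannot register a change in the trial's other wound outcome. If non-SSI events differed between arms, the conclusion on healthcare cost could be too favourable or too unfavourable to the coated suture, and nothing in the reported total would show it. The formula and the recording trigger are both fixed in the protocol, so this is a stated rule and not a detail awaiting a later document.

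**Working it through.** The protocol gives no unit costs, no cost result and no rate for non-SSI wound complications, so there is no cost figure to reproduce. The check compares the stated rules with each other and then shows, under labelled assumptions, what the size depends on.

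**Step 1. Which wound events can fall outside the SSI definition?** Under Diagnosis of SSI, a superficial infection needs purulent drainage or a positive culture. The dehiscence criterion for a deep infection does not apply when the culture is negative. So a culture-negative dehiscence that meets no other criterion is not an SSI. Nor is a superficial wound opening without pus or a positive culture. Suspected cases that are not confirmed are a third group.

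**Step 2. What does each type of woman contribute to total cost?**

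| Woman | Index stay | Drugs, tests, dressings, reintervention | Post-discharge or readmission care |
|---|---|---|---|
| Confirmed SSI | counted | counted (SSI cost) | counted (SSI cost) |
| Wound complication, not an SSI | counted (caesarean cost) | no term | no term |
| Suspected SSI, not confirmed | counted (caesarean cost) | no term | no term |

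The gap is the four empty cells. The index stay is not part of it.

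**Step 3. When does the gap bias the comparison?** Let C be the mean cost of an SSI, taken as equal in both arms. Let d be the rate of omitted events with coated suture minus the rate with control, and let r be the mean omitted cost of such an event as a fraction of C.

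- SSI rates from Sample size calculation: 9% control, 2% coated. Credited SSI saving per woman = (0.09 − 0.02) × C = 0.07C.
- In events, at 148 per arm: 148 × 0.09 = 13.3 against 148 × 0.02 = 3.0, a difference of 148 × 0.07 = 10.4.
- Omitted cost difference per woman = d × r × C.
- Omitted difference as a share of the credited saving = d × r / 0.07.

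Both d and r are assumptions, because the document supplies neither:

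| Absolute d | r = 0.1 | r = 0.5 | r = 1.0 |
|---|---|---|---|
| 0 | 0% | 0% | 0% |
| 2 points (148 × 0.02 = 3.0 women) | 0.02 × 0.1 / 0.07 = 3% | 0.02 × 0.5 / 0.07 = 14% | 0.02 × 1.0 / 0.07 = 29% |
| 5 points (148 × 0.05 = 7.4 women) | 0.05 × 0.1 / 0.07 = 7% | 0.05 × 0.5 / 0.07 = 36% | 0.05 × 1.0 / 0.07 = 71% |

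The sign follows d. If the events are more frequent with the coated suture, the saving is overstated; if less frequent, it is understated. The table shows how sensitive the result is. It is not an estimate.

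**The case against.** The strongest reply is that this is a choice of scope. The economic measure is cost per SSI prevented, and an SSI-related numerator suits that denominator. The document's stated mechanism is bacterial colonisation of the suture, and it gives no reason to expect non-infectious complications to differ between arms. If they do not differ, the omitted term cancels. The point about cancellation stands in full. The scope argument would settle the matter only if the outcome and hypothesis were worded as SSI-related cost, and they are not.

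Several stronger readings are tempting, and the documents do not support them:

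- *That no resource use is captured without an SSI.* Hospital stay is in the caesarean cost of every woman, so a longer index stay caused by any wound problem is counted. The form also has a hospital cost section whose items cannot be seen.
- *That the missing data are certain to be lost.* More may be collected than the text lists, and the protocol draws on hospital records. Even so, the stated formula would make no use of the extra items.
- *That dehiscences and drained collections go uncosted as a class.* Many would qualify as SSI, through pus, a radiologically detected abscess, dehiscence with symptoms unless the culture is negative, or a physician's diagnosis of deep infection.
- *That all wound healing complications are omitted.* The term is not defined in the visible text, and any that are also SSIs are already costed.
- *That the cost result favours the coated suture.* Nothing in the document indicates a direction.

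The wound-care sentence, "A care bundle with fixed cost will be also used for wound care. The overall cost per SSI is calculated by the following formula", is loosely worded and might be read as covering all wound care. It stands under the SSI cost heading and feeds the per-SSI formula, so it does not close the gap.

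**Conclusion.** The point holds in a limited form. Following the stated formula gives an incomplete hospital cost. It omits drugs, tests, dressings, reintervention and post-discharge or readmission care for wound events that are not SSIs and for suspected SSIs that are not confirmed. That does not match an outcome defined from the hospital's perspective or a hypothesis about healthcare cost.

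The effect on the between-arm comparison is 0% if such events are balanced in frequency and cost. Otherwise its size and direction cannot be derived from the document; the percentages above rest wholly on assumed values of d and r, on equal SSI cost in both arms, and on the planning rates. The primary outcome is unaffected. The mismatch is worth correcting because the correction is cheap and is best made before data are collected.

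**What to change.** In Costs estimation, define total cost as caesarean cost, plus SSI cost, plus the cost of non-SSI wound complications and unconfirmed suspected SSIs. Build the new term from the items already used for an SSI: care bundle, drugs, investigation tests, reintervention and hospital stay beyond the index stay. In Data collection and management, change the trigger so that these items are recorded for every woman with any wound complication or suspected SSI, confirmed or not. Define wound healing complications in Outcomes and say how they relate to SSI, so that no event is costed twice. Keep the SSI-only total as a secondary line.

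If the sponsor prefers the narrower scope, relabel the cost outcome and the second hypothesis as SSI-related cost.

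The change costs one formula term and existing form items completed for some additional women. It needs no new visits or procedures. The downside is slightly more data entry and a more variable cost total.

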**Hypotheses**

- The use of antibacterial skin sutures reduces the rate of SSI after ceasarian delivery.

-Triclosan coated suture reduce healthcare cost.

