***Sample size calculation:***

The rate of SSI after Caesar section in our center was 9% in 2019. Thus, the assumed expected wound infection rates were 2% with coated suture use versus 9% for the control group. On the basis of a two-sided chi2 test for equality of proportions, the study was expected to have 80% power to detect a relative risk reduction of 5%. A total of 296 patients were estimated to be needed, that is 148 in each arm. The G*Power 3.1.9.6 software (Heinrich-Heine University, Dusseldorf, Germany) was used to calculate the sample size.

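### The ratio labelled cost per SSI prevented has its denominator in the wrong order, so its sign is reversed whenever the coated suture reduces infections

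*Protocol*

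**What the plan says.** The Protocol's Costs estimation section builds the economic outcome in steps. It defines a caesarean cost per procedure. For infection cost it says "The overall cost per SSI is calculated by the following formula" and then lists the components. It adds the two: "The total cost is the sum of cesarian cost and SSI cost", repeated as "Total cost = Cesarian cost + SSI cost". It closes with the comparative measure, printed just above the Limitations heading: "Cost per SSI prevented = TC (Vicryl Plus) – TC (Vicryl) / SSI (Vicryl Plus) – SSI (Vicryl".

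Three other places bear on the signs:

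- Hypotheses, clinical: "The use of antibacterial skin sutures reduces the rate of SSI after ceasarian delivery".
- Hypotheses, economic: "Triclosan coated suture reduce healthcare cost".
- Sample size calculation: "the assumed expected wound infection rates were 2% with coated suture use versus 9% for the control group".

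The Outcomes section names cost impact, from the hospital's perspective, as a secondary outcome. Nowhere does the protocol state a sign convention for the ratio or correct the formula.

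**The concern.** The label and the formula disagree. A cost per infection prevented needs the number or proportion of infections prevented as its denominator, that is, control minus coated. The formula takes coated minus control. If the trial finds what it expects, the denominator is negative and the ratio changes sign.

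The sign matters in a measure of this kind. A positive value is read as the price paid to avoid one infection, and a negative value as money saved for each infection avoided. Applied as written, the formula would present a cost-saving, effective suture as costing money, and an effective but dearer suture as saving it. A hospital that read only this ratio would draw the wrong conclusion about value for money.

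**Working it through.** The protocol prints a formula and no result, so there is no figure to reproduce. The check is to evaluate the formula.

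**Inputs from the Protocol**
- SSI proportions (Sample size calculation): 0.02 with Vicryl Plus, 0.09 with Vicryl.
- Arm size (Sample size calculation): 148.
- Expected direction (Hypotheses): fewer infections and lower cost with Vicryl Plus.

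**Assumed inputs**
- The protocol gives no costs. I take a mean total cost (TC) of 500 units per woman with Vicryl, and a difference of 10 or 20 units per woman in either direction with Vicryl Plus. The base of 500 cancels in the bracketed forms.

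**Denominators**
- As written: SSI(Plus) - SSI(Vicryl) = 0.02 - 0.09 = -0.07.
- As the label requires: SSI(Vicryl) - SSI(Plus) = 0.09 - 0.02 = +0.07.

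**Ratio with the evident brackets, [TC(Plus) - TC(Vicryl)] / denominator**

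| Cost difference per woman (assumed) | As written (÷ -0.07) | Matching the label (÷ +0.07) |
|---|---|---|
| -20 (saves) | +285.7 | -285.7 |
| -10 (saves) | +142.9 | -142.9 |
| +10 (dearer) | -142.9 | +142.9 |
| +20 (dearer) | -285.7 | +285.7 |

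The absolute value is the same in each row and only the sign differs. Changing the assumed costs rescales the entries but leaves the reversal in place.

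**The same check on arm totals.** At 148 per arm the planning rates give 0.09 × 148 = 13.3 and 0.02 × 148 = 3.0 infections, say 13 and 3. A difference of 20 per woman is 148 × 20 = 2,960 per arm.
- Saving, as written: -2,960 / (3 - 13) = +296. With the denominator reversed: -296.
- Dearer, as written: +2,960 / (3 - 13) = -296. With the denominator reversed: +296.

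(These 296 are cost units; the match with the total sample size is an accident of the assumed 20 units.)

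**Strictly literal reading, without brackets.** Only TC(Vicryl)/SSI(Plus) is divided. With TC of 480 and 500: 480 - 500/0.02 - 0.09 = 480 - 25,000 - 0.09 = -24,520.09. This mixes a cost, a cost per unit of risk and a risk, and has no meaning.

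**Condition.** The reversal needs SSI(Plus) < SSI(Vicryl). If Vicryl Plus does not reduce infections, none are prevented and the label fits neither form.

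**The case against.** The strongest defence is that taking intervention minus comparator above and below the line is the ordinary form of an incremental ratio. With brackets, the formula is a valid incremental cost per additional infection, and a new label would cure the conflict as well as a new denominator would. That is true, and it means the fault is a mismatch between label and formula. The mismatch remains, because the protocol calls the result a cost per infection prevented.

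The second defence concerns consequence. The economic hypothesis asks whether cost falls. The numerator answers that with the correct sign, and anyone who holds both arms' costs and infection rates can put the ratio right at once. This stands. A reader might infer that the plan gets the direction of the whole cost question wrong, and the documents do not support that: one derived summary has the wrong sign.

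Other stronger readings also go further than the text:

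- **Missing brackets.** The intended grouping is obvious, and a stacked fraction may have been flattened when the PDF was read. The brackets should be printed, but their absence is no separate error.
- **Averted infections never reach the numerator.** A reader might infer this because a cost per procedure is added to a cost per SSI. The natural reading is that a woman has an SSI cost only if she has an SSI. The Data collection and management section supports it, since SSI resources are recorded only when an SSI is present.
- **Unequal arms drive the difference.** Equal arms are planned ("A total of 296 patients were estimated to be needed, that is 148 in each arm"), and nothing says that arm sums will be compared.
- **Hospital days are counted twice.** Hospital stay appears in both cost components, which fits a delivery stay plus a separate SSI-related stay. Double counting is not shown.
- **No intervals are given for the ratio.** That is commonly left to the SAP, which is not shown.

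**Conclusion.** The point holds in a limited form. As labelled, the ratio has the wrong sign whenever Vicryl Plus has fewer infections, which is the result the trial hypothesises and plans for (a difference of -0.07 at 2% against 9%). A cost-saving suture would then show a positive cost per SSI prevented, and a dearer one an apparent saving.

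The conclusion rests on supplying the evident brackets and on infections being fewer with Vicryl Plus. It does not rest on the cost figures used for illustration. The magnitude of the ratio, the separate cost difference and the primary outcome are untouched. Severity is minor to moderate: a formula for a named secondary outcome is wrong as written, and it is easily put right.

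**What to change.** Replace the formula with:

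cost per SSI prevented = [TC(Vicryl Plus) - TC(Vicryl)] / [SSI(Vicryl) - SSI(Vicryl Plus)]

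Add one sentence of definition: TC is the mean total cost per woman in the arm, with SSI cost set to 0 for a woman without an SSI, and SSI is the proportion of women infected in the arm.

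Add one sentence on reporting: show the ratio beside the cost difference and the difference in SSI proportions, and if Vicryl Plus is both cheaper and has fewer SSIs, call it dominant. This is needed because even the corrected ratio is negative in two opposite situations: cheaper with fewer infections, and dearer with more.

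The cost is a short edit to the Costs estimation section. It needs no further data, patients or visits and does not touch the primary analysis. It is best made before any cost results are compared between arms.

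### If both hypotheses hold, the cost-per-SSI-prevented ratio, the only between-arm cost statistic named, cannot be interpreted; the cost and SSI differences should be reported separately

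*Protocol*

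**What the plan says.** The Hypotheses section of the protocol makes two claims: "The use of antibacterial skin sutures reduces the rate of SSI after ceasarian delivery" and "Triclosan coated suture reduce healthcare cost". The Outcomes section lists as a secondary outcome "The cost impact of triclosan coated suture use from a hospital perspective".

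The Costs estimation section then builds the cost variable. The caesarean part is "Cesarian cost = Bundle cost + Suture material cost + Hospital stay cost". A separate SSI cost adds care bundle, drugs, tests, reintervention and stay. The two are summed: "Total cost = Cesarian cost + SSI cost". The section ends, just above Limitations, with the one statistic that compares the arms on cost. It opens "Cost per SSI prevented = TC (Vicryl Plus" and runs in full "Cost per SSI prevented = TC (Vicryl Plus) – TC (Vicryl) / SSI (Vicryl Plus) – SSI (Vicryl", with a closing bracket after the last term.

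Nothing says how to read that ratio if the coated suture is cheaper as well as more effective. The section gives no unit costs.

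**The concern.** A cost per event prevented is the price paid for extra benefit, so it has a clear meaning when the more effective arm is also the dearer one. The protocol expects the opposite on cost. If both hypotheses are confirmed, no price is being paid and the coated suture simply dominates. The ratio can still be computed, but its size then mixes a saving and a benefit that both favour the same arm, and a larger or smaller value is not consistently better.

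The second hypothesis would then be reported through a figure that does not answer it. That hypothesis concerns a difference in cost, which enters the named statistic only as a numerator.

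This is separate from the missing brackets and the order of subtraction in the denominator. The difficulty remains once those are repaired.

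**Working it through.** **Inputs.** From Sample size calculation: "the assumed expected wound infection rates were 2% with coated suture use versus 9% for the control group", 148 women per arm, two-sided chi-square test, 80% power. Alpha is not stated; 0.05 is assumed. All cost figures below are assumed money units for illustration, because the protocol gives none.

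**The plan's own figure.** The arcsine formula gives h = 2·arcsin(√0.09) − 2·arcsin(√0.02) = 0.3256, and n = 2 × ((1.960 + 0.842)/0.3256)² = 148.1 per arm. This agrees with the stated 148. The point does not depend on the sample size formula.

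**Step 1: sign.** Take the ratio with brackets supplied and the denominator turned round: (TC Plus − TC Vicryl) / (SSI Vicryl − SSI Plus). Expected SSIs are 148 × 0.09 = 13.32 and 148 × 0.02 = 2.96, so 10.36 are prevented.

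- Vicryl Plus saves 1000 in total and prevents 10.36 SSIs: −1000/10.36 = −96.5.
- Vicryl Plus costs 1000 more and has 10 more SSIs: 1000/(−10) = −100.

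The best and the worst outcome for the coated suture give nearly the same number. With the denominator in the printed order (brackets supplied) they become +96.5 and +100, which are no easier to tell apart.

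**Step 2: size, with the saving held fixed at 1000.**

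| SSI rate, Vicryl Plus | SSIs prevented | Corrected ratio |
|---|---|---|
| 2% | 10.36 | −96.5 |
| 4% | 7.40 | −135.1 |
| 6% | 4.44 | −225.2 |
| 8% | 1.48 | −675.7 |

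Here the weaker suture shows the larger apparent saving per SSI.

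**Step 3: size, with the saving tied to SSIs.** Total cost contains SSI cost, so the numerator also moves with the effect. Let s be the difference in caesarean cost per woman (Vicryl Plus minus Vicryl), c a constant cost per SSI, and RD the risk difference. The cost difference per woman is s − c·RD, and the corrected ratio is s/RD − c.

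| s | c | RD 7 points | RD 3 points | The weaker suture looks |
|---|---|---|---|---|
| 5 | 300 | −228.6 | −133.3 | worse |
| 0 | 300 | −300.0 | −300.0 | the same |
| −2 | 300 | −328.6 | −366.7 | better |

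Vicryl Plus is cheaper with fewer SSIs in all six cells, yet the direction of the ratio depends on the sign of s. Because caesarean cost includes hospital stay as well as suture material, s need not equal the suture premium, and the protocol does not fix its sign.

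**Step 4: precision of the denominator.** SE = √(0.09 × 0.91/148 + 0.02 × 0.98/148) = 0.0262. The 95% CI is 0.070 ± 1.96 × 0.0262, that is 1.9 to 12.1 points. The exact two-binomial power of the uncorrected chi-square test at 148 per arm is 78.9%, so about 100 − 78.9 = 21% of trials run at the planning rates would have a non-significant SSI difference. A Fieller-type interval for the ratio is then unbounded.

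**The case against.** The strongest reply is that this is a two-arm trial with one comparison. No threshold, ranking or decision rule is attached to the ratio. The secondary outcome is cost impact, not cost-effectiveness, and the difference in total cost is already the explicit numerator, so the second hypothesis can be answered from quantities the protocol defines. Methods for intervals, dominance rules and net benefit commonly sit in a SAP, which is not shown.

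Much of this stands. The cost difference can be derived without new data, the absence of interval methods is not held against the protocol, and the unbounded interval describes how such a ratio behaves, not an interval the protocol specifies. What the reply does not remove is that the protocol does name a between-arm cost statistic, and the one it names fits its own hypotheses badly.

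Two stronger readings are tempting and should be resisted. A reader might infer from Step 2 that a less effective suture would always look better. Step 3 shows otherwise: with a positive s and a constant cost per SSI it looks worse. A reader might also divide the confidence limits, 12.1/1.9, and conclude that the denominator alone moves the ratio about 6.5-fold. That freezes a numerator which itself contains SSI cost, so the actual spread depends on prices the documents do not give.

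**Conclusion.** The point holds as a minor one on a secondary outcome. If Vicryl Plus proves cheaper with fewer SSIs, the size of the planned ratio cannot be interpreted, and its sign does not distinguish that result from dearer with more SSIs, even after the formula's brackets and denominator order are corrected. Whether a weaker suture would look better, the same or worse depends on unit costs that are not given.

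The denominator is a difference of about 10.4 SSIs out of about 16.3 expected in total, with a 95% CI of about 1.9 to 12.1 points. About one trial in five at the planning rates would leave a Fieller-type interval for the ratio unbounded.

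This rests on the planning rates, 148 analysed women per arm, an assumed two-sided alpha of 0.05 and, for the ratios, illustrative costs. The primary outcome, the sample size and the data collected are unaffected.

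**What to change.** In Costs estimation, name as the cost result that answers the second hypothesis the difference in mean total cost per randomised woman (Vicryl Plus minus Vicryl) with a 95% CI, reported beside the SSI risk difference with its CI. State that cost per SSI prevented is given only if Vicryl Plus costs more and has fewer SSIs. If it costs less and has fewer SSIs, report dominance together with the two differences. Net benefit over a stated range of values per SSI avoided is an optional addition and can be left to the SAP.

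The cost is a few lines of wording and a little programming, with no new data. The one small loss is that there is no headline cost-per-SSI figure when the coated suture saves money. The brackets and the denominator order need their own correction in the same formula.
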